Commonly cited reasons for the lack of comprehensive sexual health care within oncology include limited access to specialty services, provider and patient discomfort in discussing sexual health, and appointment time constraints [24,25]. Delivering fully automated care via the internet can help alleviate these barriers to care by providing evidence-based education and behavioral strategies privately and on demand, anywhere an internet connection exists [26-28]. Comprehensive sexual health interventions have been demonstrated as effective when delivered remotely; however, the substantial time requirements of these multicomponent programs have been a leading barrier to enrolling and retaining survivors in care [28-30]. Maximizing the population-wide impact of sexual health interventions for survivors of breast cancer will require minimizing intervention requirements, without compromising the overall intervention efficacy. More efficient interventions may attract and retain more survivors to benefit from care.

A major gap in the literature regarding the efficacy of individual sexual health components has limited the development of more efficient sexual health treatments for survivors of breast cancer [29]. Because of the complex biopsychosocial nature of sexual health, interventions to improve sexual health after cancer typically include multiple therapeutic components. Leading clinical oncology organizations recommend that women are educated about the effects of cancer on their sexual response cycle, as well as interventions to improve intimacy and relationship concerns [21,31]. Communication skills training is critical to help survivors overcome the barriers of stigma to advocate for their sexual health needs [1]. Because interventions tested in this area to date have tended to test multiple components packaged together and in differing combinations across trials, it has been impossible to differentiate which components work, establish why those components work, or identify for whom different components work best. Addressing these gaps will help promote the development of more efficient, effective, and personalized interventions.

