#### Sample Size and Power Analysis

This factorial trial has been powered to detect a small-to-medium effect size (ie, Cohen *d*=0.30) of intervention components on sexual morbidity outcomes. This represents the smallest effect size that the study team determines would offset the required resources of an intervention component to be delivered to and completed by participants in an optimized intervention. Determined using the MOST R package [60] *FactorialPowerPlan* function (R version 3.6.2; R Foundation for Statistical Computing), 247 survivors of breast cancer would be needed to detect Cohen *d*=0.30 of change in sexual distress from baseline to 24-week assessment (measured by FSDS-DAO) at 80% power with α=.05 for all main effects and interaction effects of the intervention components. In a factorial experimental design with only 2 levels per factor, the power to detect main effects and interaction effects is equal [39,61]. This power analysis assumes a pretest-posttest correlation in sexual distress of *r*=0.65, which is supported by data from the investigators’ prior research (Female Sexual Distress Scale pretest-posttest *r*=0.73; N=28) [32] and by Female Sexual Distress Scale validation data (pretest-posttest *r*=0.62; N=318) [49]. The effect size of Cohen *d*=0.30 is reasonable to expect from intervention components, given that prior randomized controlled trials of interventions containing the components demonstrated large effects on sexual distress relative to control (Cohen *d*=0.87 and Cohen *d*=0.59) [28,32]. Conservatively accounting for an estimated 20% attrition (based on the investigators’ past trials) [32,42,62] and rounding up to achieve a balanced number of participants per condition, 320 survivors will be randomized in the trial (247/0.80=309 rounded to a total N=320, for n=20 per each of the 16 factorial conditions).

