### Data Analysis Plan

#### Overview

In accordance with the NIH requirement, a Data Safety and Monitoring Plan has been established to guide study oversight and ensure the safety of participants and data validity and integrity. Summaries of primary and secondary measures will be reviewed for completeness every 6 months by the WF NCORP RB Data Safety Monitoring Board, along with other key study metrics such as recruitment, retention, patient characteristics, and adverse events. More details about trial oversight and monitoring are available in Multimedia Appendices 3 and 4.

Study methods have been designed to avoid missing data, including efforts to retain participants with incentives and assessment reminder protocols, as well as requiring responses to all items on web-based assessment questionnaires. As it is not possible to entirely avoid missing data, restricted maximum likelihood estimation will be used to address missing data in analyses under a missing at random (MAR) assumption [63-65]. Proposed analyses are robust against MAR data [63,64]. The National Academy of Sciences guidelines for missing data will be followed [64], and the impact of missing data on study conclusions will be explored with sensitivity analyses. Specifically, attrition rates across study conditions will be compared. If a particular condition has a markedly higher dropout rate, baseline covariates that predict attrition will be identified in secondary analyses. Variables determined to predict loss to follow-up will be included in sensitivity analysis models to satisfy the conditions described by Little and Rubin [65] for data to be considered MAR.

Primary analyses will be intention to treat, meaning that the randomized condition assignment will be included in models regardless of whether the participant completes their assigned Cores or not. Sensitivity analyses will examine the effects by whether assigned Cores are completed or not. All participants with at least 1 follow-up assessment will be included in analyses. All tests of hypotheses and reported P values will be 2 sided.

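### The attrition check works on 16 cells of 20 women, not on the component contrasts, and makes the search for predictors of dropout depend on one cell standing out

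*Protocol article*

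**What the plan says.** The Data Analysis Plan (Overview) handles missing outcomes by restricted maximum likelihood (REML) under MAR. For sensitivity analysis it specifies that "attrition rates across study conditions will be compared", followed by a conditional step: "If a particular condition has a markedly higher dropout rate, baseline covariates that predict attrition will be identified in secondary analyses". Variables found to predict loss then enter the sensitivity models, and the stated purpose is to meet the conditions under which the data may be treated as MAR.

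Trial Design and Sample Size and Power Analysis make clear what a condition is: one of the 16 cells of the 2×2×2×2 factorial, with 20 women in each. Primary Objective Analyses uses a different unit. Main and interaction effects are averaged over cells, and a component is provisionally kept if its main effect reaches Cohen d of 0.3. With 320 women and two levels per component, each main effect compares 160 with 160.

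**The concern.** The attrition check and the estimates it is meant to protect use different units. If assignment to a component affects follow-up, the effect is spread over eight cells against the other eight. It is a contrast between halves of the trial, not one outlying cell. A rule that looks for one high cell of 20 is weak against that pattern and easily triggered by chance.

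The conditional step is the more important fault. A baseline variable can predict dropout strongly when every cell loses the same number of women. Whether such variables belong in the sensitivity model therefore has nothing to do with whether one cell looks high. If none does, the plan as written does not look for them, and the sensitivity analysis that it links to MAR is not run.

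A dropout pattern by component is plausible here. The Background says that "the substantial time requirements of these multicomponent programs have been a leading barrier to enrolling and retaining survivors in care", and in this trial the number of Cores is set by randomization. What is at stake is how far an inclusion decision near the 0.3 threshold can be defended.

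**Working it through.** **Inputs from the protocol article.** Effect size d = 0.30, pre-post correlation r = 0.65, 80% power, α = .05, two-sided tests, 20% attrition, 247 evaluable, 320 randomized, 16 cells of 20.

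**Assumptions, not in the article.** The cut-off for a markedly higher rate (35% to 50% shown), the size of a component-related dropout gap, and how much worse dropouts do than the model predicts.

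**1. The plan's own sample size.** SD of change = √(2(1 − 0.65)) = 0.837 outcome SDs. Total N = 4(1.96 + 0.8416)² × 0.70 / 0.30² ≈ 244, or 246 after rounding up to whole women per group. The noncentral-t version gives 247, as stated. Then 247/0.80 = 309, raised to 320 = 16 × 20. The sample size is reproduced and is not in question.

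**2. How often a cell looks high.** Dropouts in a cell follow Binomial(20, p). With p = 0.20 in every cell, P(at least one cell reaches k) = 1 − (1 − P(X ≥ k))^16. If one component shifts dropout to 15% versus 25%, it is 1 − (1 − P₁₅)⁸(1 − P₂₅)⁸, where P₁₅ and P₂₅ are the single-cell tail probabilities at those rates.

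| Cut-off | P(X ≥ k) at 20% | Some cell reaches it, 20% everywhere | Some cell reaches it, 15% vs 25% |
|---|---|---|---|
| 35% (k = 7) | 0.0867 | 77% | 88% |
| 40% (k = 8) | 0.0321 | 41% | 60% |
| 45% (k = 9) | 0.0100 | 15% | 29% |
| 50% (k = 10) | 0.0026 | 4% | 11% |

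With no true difference, the highest of the 16 cells averages 37% and the lowest 6% (simulation). No cut-off separates the last two columns well. A low one fires mostly on chance. A high one stays silent in most trials that have a real 10-point gap (71% at the 45% cut-off, 89% at 50%).

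**3. Power by unit of comparison.** The 16-cell test is a 15-df chi-square (simulated). The component test compares two proportions, 160 versus 160.

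| Dropout by component level | 16-cell test | 160 vs 160 |
|---|---|---|
| 15% vs 25% | 20% | 61% |
| 14% vs 26% | 30% | 77% |
| 10% vs 30% | 83% | over 99% |

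For the first row, the standard error of the difference is √(0.2 × 0.8 × 2/160) = 0.0447 under no difference and 0.0444 under the gap. Power is Φ((0.10 − 1.96 × 0.0447)/0.0444) = 0.61. The component comparison reaches 80% power at a gap of about 12.5 points. A single cell of 20 against the other 300 would need about 51% versus 20%.

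**4. Size of the possible bias.** If MAR holds given the modelled data, the bias is zero whatever the gap. If dropouts at both levels do D SD worse than the model predicts, the bias is about (gap in dropout) × D. For a 10-point gap:

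- D = 0.25: 0.10 × 0.25 = 0.025 SD
- D = 0.50: 0.10 × 0.50 = 0.05 SD
- D = 1.00: 0.10 × 1.00 = 0.10 SD

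That is 8% to 33% of the 0.30 threshold. The standard error of a main effect is 2 × 0.837/√247 = 0.107 SD, so the bias is at most about one standard error.

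Equal dropout is not a guarantee of safety. At 20% in both levels, with dropouts 0.5 SD worse than modelled at one level only, the bias is 0.20 × 0.5 = 0.10 SD. This is a further reason not to make the covariate model depend on observed rates.

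**The case against.** The case on the other side is substantial.

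- **Unequal dropout is not in itself bias.** The primary model is REML under MAR with randomized assignment included. A reader might infer that component-level dropout does bias the estimates. The article does not support that: a gap is neither sufficient nor necessary for bias. This stands.
- **The cut-offs are supplied here.** No threshold is given, and the analysis plan, not shown, may define one. At 50% the false-alarm rate is only 4%. This stands, but a threshold would change neither the unit nor the conditional step.
- **The check is not blind.** A 10-point component gap raises the firing rate at the 40% cut-off from 41% to 60%, and a 20-point gap is found 83% of the time by the 16-cell test. To say that it misses component-level dropout would be too strong; it discriminates poorly for moderate gaps.
- **A false alarm costs little.** It only adds covariates to a sensitivity model. This stands, and so the harm lies in the silent trigger.
- **The Background concerns retention in care.** A reader might take it as the plan's own premise that burden causes missing 24-week outcomes. It is not. Women who stop using their Cores remain in the intention-to-treat analysis, gift cards are tied to assessments, and assessment reminders are separate from program prompts. Burden-related missingness is plausible, no more.
- **No analysis outside MAR is described.** The article commits to recognized missing-data guidelines and to sensitivity analyses, and such detail is commonly left to the analysis plan. Its absence here is not a fault.

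**Conclusion.** The point holds in a limited form. The article states a rule that checks attrition on the wrong unit and makes a MAR-supporting step depend on a signal unrelated to whether that step is needed. For a 10-point gap by component, power falls from 61% to about 20% when the comparison is made over 16 cells. With no gap at all, chance alone takes some cell to twice the average rate in 41% of trials.

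The effect on conclusions is conditional and modest: nothing if MAR holds given the modelled data, and 0.025 to 0.10 SD under the assumed departures, enough to matter only for a component near the 0.30 threshold. Only the sensitivity analyses are affected. The sample size and the primary analysis stand. The change is worth making because it costs almost nothing and removes a rule that can leave a stated safeguard unused.

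**What to change.** 1. Compare 24-week completion by component level with an effect-coded logistic model containing the four factors and key interactions. Report differences with confidence intervals; at 20% dropout the 95% half-width is about 1.96 × 0.0447 = 8.8 percentage points. The 16-cell rates can stay as a descriptive table.
2. If the number of assigned Cores is of interest, fit it in a separate model. Every woman receives one Essentials Core, so the count is one plus the three on/off components. It is a linear function of factors already in the model and cannot be added to it.
3. Identify baseline predictors of attrition and fit the sensitivity model that includes them whatever step 1 shows, and delete the condition about one markedly higher cell.
4. Optional, and possibly already in the analysis plan: a delta-adjusted analysis that shifts missing 24-week FSDS-DAO scores and reports the shift at which an inclusion decision changes.

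The primary REML analysis is untouched. The cost is a few sentences in the plan and a little extra analysis of data already collected.

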## Methods

### Ethical Considerations

The study protocol has been reviewed and approved by the National Cancer Institute (NCI) Central Institutional Review Board (CIRB; WF-2202 initially approved on December 1, 2023). Study modifications will be reviewed and approved by the NCI CIRB. Participating study sites and their local institutional review boards will be notified of any modifications. Deidentified data sets used in primary publications will be transferred to the National Clinical Trials Network and NCI Community Oncology Research Program (NCORP) Data Archive in accordance with the agreement between Wake Forest (WF) NCORP Research Base (RB) and NCI. The internet intervention platform hosting the Sexual Health and Intimacy Enhancement (SHINE) intervention is managed by the University of Virginia (UVA) and was designed to support projects that contain protected health information that are subject to compliance with federal and state regulations. Access to data will be in accordance with the Health Care Financing Administration’s Internet Security Policy and the Health Insurance Portability and Accountability (HIPAA) Act of 1996. The database servers and web servers are backed up daily and are protected from threats by regular maintenance and the application of hotfix and security patches when released. Security policies are in place with UVA to ensure that access to database repositories and web application server environments is limited. On completion of the trial, summary results will be submitted to ClinicalTrials.gov in accordance with National Institutes of Health (NIH) policies [35]. No participant identifiers will be published.

During the informed consent process, potential participants are informed that this study aims to determine whether an internet-delivered program can help survivors of breast cancer manage cancer-related sexual concerns. Under a waiver of documentation of consent, participants will provide either signed informed consent or verbal informed consent that is documented by the enrolling research staff member. The NCI CIRB–approved informed consent form will be made available open-access with other study materials. Participants will receive a US $50 e-gift card for completing the 12-week assessment and a US $75 e-gift card for completing the 24-week assessment. On request at the end of the 24-week assessment, participants will be provided access to all the SHINE program components through the end of the grant period.

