### Intervention

Intervention components are delivered fully automated as a *Core*, or lesson, of content. Components (and component levels) to be tested are (1) education about the influence of breast cancer on sexual health, either with limited information in a static web page format in the Sexual Health Essentials-Standard Core or more comprehensive information through an interactive web program in the Sexual Health Essentials-Enhanced Core; (2) communication skills training for discussing sexual concerns with one’s health care team in the Health Care Discussions Core; (3) communication skills training for discussing sexual concerns with one’s intimate partner in the Partner Conversations Core; and (4) intimacy promotion skills training in the Intimacy Insights Core. All participants will receive 1 of 2 Sexual Health Essentials Cores (ie, standard [component level=low] or enhanced [component level=high]) given that survivorship care guidelines recommend that all survivors receive education about the influence of cancer treatment on sexual health [21]. For the 3 remaining components, participants will either receive the Core (component level=on) or not receive the Core (component level=off; see Figure 2 for factorial design and Multimedia Appendix 2 for additional Core details).

The Sexual Health Essentials-Enhanced, Health Care Discussions, Partner Conversations, and Intimacy Enhancement Cores each deliver content as stand-alone, web-based programs. These Cores were developed following the Model for Internet Interventions [46] and user-centered design practices to be highly engaging, using interactive elements, audiovisuals, and tailoring. Cores were developed with a team of software engineers and consultants in user interface, user experience, and instructional design. Core content was refined through iterative feedback from survivors of breast cancer. The Sexual Health Essentials-Standard Core provides education via a traditional web page with no tailoring or interactive elements.

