#### Engagement and Acceptability

Participants’ engagement with the SHINE intervention will be characterized by metrics including the number of log-ins and Core completion rates (collected automatically by the SHINE intervention platform). At the 12-week assessment, participants will rate their satisfaction with the SHINE intervention Cores (Client Satisfaction Questionnaire-8) [58] and perceived usability of the Cores (Internet Intervention Utility Questionnaire) [59].

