### Exploratory Analyses

We will examine survivors’ intervention engagement and acceptability. Means and SDs or frequencies, as appropriate, of user engagement metrics will be reported. Whether log-ins differ by components will be tested using the GLM approach as described for the primary objective analyses. The influence of engagement on the change in sexual morbidity outcomes will also be tested by extending GLM models from the primary objective analyses to include the interaction effects between intervention components and engagement. Users’ ratings of Core usability and satisfaction will also be reported.

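### The by-completion and engagement analyses condition on behaviour after randomization, so they can credit an inert component with an effect; the primary analysis and the package decision are not affected

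*Protocol article*

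**What the plan says.** The main analysis follows randomization. Under Data Analysis Plan, Overview: "Primary analyses will be intention to treat, meaning that the randomized condition assignment will be included in models". Primary Objective Analyses then selects components from the main and interaction effects on the FSDS-DAO, with a threshold of d≥0.3.

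Two further analyses use behaviour observed after randomization:

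- Overview, Data Analysis Plan: "Sensitivity analyses will examine the effects by whether assigned Cores are completed or not". No comparator, model or estimator is named.
- Exploratory Analyses: the influence of engagement on change in the outcomes is tested by "extending GLM models from the primary objective analyses to include the interaction effects between intervention components and engagement". Under Measures, engagement is characterized by "metrics including the number of log-ins and Core completion rates". The same section also plans a prior question: "Whether log-ins differ by components will be tested using the GLM approach".

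Two design facts bear on both. For the three on/off components, "participants will either receive the Core (component level=on) or not receive the Core" (Intervention). Access to unassigned Cores comes only afterwards: "On request at the end of the 24-week assessment, participants will be provided access to all the SHINE program components" (Ethical Considerations).

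**The concern.** A woman who finishes a Core probably differs in motivation, health or relationship from one who does not. If those traits also bear on change in sexual distress, a contrast by completion mixes the Core's effect with the kind of woman who completes it. Randomization gives no protection, because the women at the *off* level who would have completed the Core cannot be picked out. Completing a later Core also depends on first finishing the Essentials Core, whose version is itself randomized, so completers may differ between the education levels.

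The engagement model has a related difficulty. Log-ins may be a consequence of assignment, as the plan recognizes by testing for it, and the model then conditions on them.

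At stake is interpretation: a component with no effect by intention to treat could be reported as working when used, although the design does not support that statement.

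**Working it through.** **Inputs from the protocol article (Sample Size and Power Analysis).** d=0.30, 80% power, two-sided α=0.05, pretest-posttest r=0.65, 20% attrition, N=320.

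**The plan's own figure.** In units of the baseline SD, the change score has SD √(2(1−0.65)) = √0.70 = 0.837. The number per level is 2(1.96+0.842)²×0.70/0.30² ≈ 122.1, so 123, or 246 in total. The noncentral-t version gives 247, as stated. 247/0.80 = 309, rounded up to 320. The sample size reproduces and is not in dispute. Expected at 24 weeks: 320×0.80 = 256, or 128 per component level.

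**Bias of a split by completion when the Core is inert.** Assumptions not in the documents: completion proportion p, and correlation ρ between the underlying tendency to complete and improvement (normal model). With φ the standard normal density at the cut-point z for p:

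- completers minus unassigned = ρ × 0.837 × φ(z)/p
- non-completers minus unassigned = −ρ × 0.837 × φ(z)/(1−p)

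At p=0.70, ρ=0.3, φ(z)=0.348:

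- completers: 0.3×0.837×0.348/0.70 = +0.12
- non-completers: −0.3×0.837×0.348/0.30 = −0.29
- gap: about 0.42

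Over the assumed range, the completer bias runs from 0.2×0.837×0.280/0.80 = 0.06 (p=0.80, ρ=0.2) to 0.4×0.837×0.399/0.50 = 0.27 (p=0.50, ρ=0.4).

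**Simulation at the trial's size.** 2⁴ design, 256 analysed, all components inert, 1,500 replicates per setting. Results for 70% completion and ρ=0.3:

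| Analysis | Mean estimate (baseline SD) | Rejections at 0.05 |
|---|---|---|
| Intention to treat | 0.00 | 5% |
| Completers vs all women at *off* | 0.12 | 19% |
| As treated | 0.19 | 41% |
| Completers vs non-completers within *on* | 0.42 | 75% |
| Complier average causal effect | 0.00 | 5% |

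At ρ=0.2 the three by-completion contrasts reject in 12%, 21% and 40% of runs. Over ρ 0.1-0.4 and completion 50-90% the ranges are 5-55%, 6-83% and 12-97%. At ρ=0 all stay near nominal (4-7%).

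**Engagement as completion of the same Core.** Code the component C=±1 and completion M=0 or 1. At *off*, M is always 0, so C×M equals M for every woman. The interaction then cannot be separated from completion itself.

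**Engagement as log-ins.** Assume each extra Core raises log-ins by 0, 25 or 50%. For an inert component:

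- The component-by-log-ins interaction stays near nominal (4-7% rejections) in every setting.
- The log-ins coefficient is significant in 54-99.6% of runs at ρ 0.2-0.4.
- Where extra Cores raise log-ins (25 or 50%) and ρ is 0.2-0.4, the component effect adjusted for log-ins shifts toward harm, by 0.03 to 0.11 SD (6-15% rejections).

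**The case against.** The strongest reply is that the by-completion sentence names no estimator. This is a condensed article, the analysis plan is not shown, and a method that respects randomization would also fit the words. That stands in part: the article does not state a wrong estimator. But the sentence describes effects examined by completion status, and Exploratory Analyses does name its model, so more than missing detail is involved.

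Three stronger readings are tempting, and the documents do not support them.

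- *That an inert component will show an effect.* It can. The bias requires completion to be related to outcome and vanishes at ρ=0. Neither ρ nor the completion rate is given.
- *That the component-by-log-ins interaction produces false component effects.* In the simulation it did not. The errors fell on the log-ins coefficient and, toward harm, on the adjusted component effect.
- *That the package decision is at risk.* Selection rests on the primary model, and nothing in the article lets completion or engagement results override it. The completer-versus-unassigned bias in the assumed range also stays below the 0.3 threshold. The larger gap of 0.42 belongs to a contrast of completers with non-completers, which the article does not specify.

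It is also fair to object that dividing the intention-to-treat effect by the completion proportion is too simple here. A participant may hold up to four Cores of about 20-45 minutes each, and assigning one could lower completion of another. That stands and shapes the fix.

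**Conclusion.** The point holds as a caution about two supporting analyses. Both condition on behaviour after randomization, there is no comparable group at *off*, and the article does not say that the results are non-randomized. If completing is related to improving, an inert Core can appear to help those who finish it: by about 0.06-0.27 baseline SD against unassigned women, under assumed completion of 50-80% and correlation of 0.2-0.4. An estimator based on assignment stays near zero with nominal error in the same settings. The intention-to-treat model, the sample size and the rule for choosing the package are unaffected.

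**What to change.** 1. **By-completion analysis (Data Analysis Plan, Overview).** For the three on/off Cores, replace it with a baseline-adjusted complier average causal effect by two-stage least squares. Fit all factors jointly, with each Core's completion instrumented by its random assignment. This is feasible because women at *off* are offered the other Cores only at the end of the 24-week assessment. State the two assumptions: being assigned a Core without completing it has no effect, and assigning one Core does not act through completion of another.
2. **Education factor.** Report by intention to treat only, since both levels receive content.
3. **Engagement (Exploratory Analyses).** Keep the results as descriptive and label them non-randomized. Do not interpret causally either the engagement coefficient or a component effect adjusted for log-ins.
4. **Package decision.** State that neither analysis enters it.

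The cost is a few lines of text and standard software, with no new data. The downside is precision. In the simplest one-Core case at 70% completion, the estimate and its standard error are both multiplied by about 1/0.70 = 1.43, so the analysis adds no power over intention to treat. The estimate is also inflated if partial use has an effect.
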